Some aspects of reporting personal genetic results for familial melanoma remain to be investigated, or completely understood. Psychosocial aspects such as genetic fatalism or essentialism for this cohort has not been reported. Genetic fatalism or essentialism can be described as the belief that one has little control over health outcomes, and that personal future health is determined by their genetic code^18^. These beliefs are often associated with decreased motivation for protective health behaviour^19^. Furthermore, it is useful to identify psychological traits present in this cohort that are associated with the uptake of genetic testing, and any correlation with significant psychological impact or behaviour change. Additionally, it is unclear what impact genetic testing has in familial cases where a clear line of inherited risk is present, however no responsible mutation is identified, leaving the cause or level of personal risk unexplained. In the present study, the effect of genetic education, counselling and testing, and on genetic fatalism will be explored. Furthermore, the extent to which psychological and behavioural outcomes vary depending on whether there is an identified familial mutation will also be explored. Lastly, this study will evaluate whether the method of delivery (dermatologist compared with genetic counsellor) of genetic test results for familial melanoma influences (or is associated with) psychological and behavioural outcomes.

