# **1.2 Aims**

Primary Aim: To understand and describe the participant’s experience with genetic education, counselling and testing, and living with familial melanoma through qualitative analysis of semi-structured interviews.

Secondary Aims: To identify psychosocial and behavioural impact of genetic testing in familial melanoma, using quantitative analysis of validated questionnaires guided by the Health Belief Model as a theoretical framework. This will be achieved by;

1. Evaluate psychosocial and behavioural impact of genetic education, counselling (and testing) in individuals with a familial melanoma, regardless of whether a causal mutation has been identified.
2. Explore genetic fatalism in a subset of participants and whether they feel that genetic counselling (+/- testing) affected their beliefs.
3. Determine whether the person conducting the counselling session (genetic counsellor/dermatologist) affects psychosocial and behavioural outcomes.
4. Evaluate what psychological traits are associated with uptake of testing, psychological impact and behavioural change.
5. Assessment of the clinician training protocol, and supporting documents, for providing genetic testing.

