In most cases the second counselling session for test reporting will occur approximately. 2-3 months after their first visit. This visit will either take place at the CRF- PAH or over online video conference call using Zoom, and will take approx. 1 to 1.5 hours. The session will begin by asking the participant to complete a questionnaire with selected validated instruments (see table 1). The purpose of these questionnaires is to measure any impact from the first genetic education and counselling appointment. Once questionnaires are complete, a genetic counsellor (or trained dermatologist) from the research team will conduct the post testing genetic counselling and reporting of genetic testing results. This process includes: test results, significance for personal risk, significance for family risk, recommended preventative health behaviour and screening. The genetic counsellor or dermatologist will offer to send a report of the genetic findings to the participant’s nominated healthcare provider. At the end of the counselling session, the participant will be asked if they consent to being contacted for a phone interview at a later date.

Post genetic testing, education and counselling questionnaires will be conducted at 2 weeks, 3 months and 12 months following reporting of test results. These questionnaires will be sent using the REDCap System, which facilitates an email containing a web-link to be sent for the participant to complete the questionnaire online, at their convenience. Two reminder emails to complete questionnaires will be sent out if not completed.

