# **Participants who decline genetic testing**

Some individuals may wish to take part in the research, but don’t wish to have genetic testing. Likewise, we expect that some participants may change their mind and decline genetic testing after receiving pre-testing genetic counselling and education, or decline receiving results after previously consenting to testing. We will ask these participants to remain in the study as they are valuable to our research in understanding barriers to genetic testing. For these participants, we will still provide genetic counselling and education based on their family history, rather than genetic testing (or not provide genetic test results if testing already completed). We would ask them to still complete pre and post questionnaires that measure their knowledge and perceptions on melanoma, psychological impact, and health behaviour. In addition we have a questionnaire designed to capture the reasons and motivation behind declining to genetic testing. We will also still invite them to take part in a semi-structured interview as part of Stage 1 of the research.

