# **Dermatologist reporting genetic results**

Participants in Stage 1 of the study will be randomised to receive the genetic education, counselling and test reporting by either a genetic counsellor or a dermatologist (or dermatologically trained clinician). We will be using block randomisation, stratified by whether the participant is from a) CDKN2A positive family, or b) other familial melanoma mutation positive family, or c) no known melanoma mutation identified. Data linkage, descried in section five, will be used to identify the genetic status of past participants before randomisation to facilitate stratification.

The aim is to evaluate whether the person providing the genetic education and counselling (genetic counsellor or dermatologist), affects the psychosocial or behavioural outcomes. The dermatologists/clinician will be provided with training from genetic counsellors prior to providing genetic education, counselling and test reporting to participants. Questionnaire data collected throughout stage 1 of the study will be used to analyse any significant differences in psychosocial or behavioural outcomes.

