# **Data Analysis**

*7.1 Stage 1: Pre and post genetic counselling questionnaires*

All questionnaires used in Stage 1, are previously validated, with recommended protocols for quantitative analysis. In some cases, questionnaire responses will be pooled within previously defined groups (i.e. *CDKN2A* positive, other germline mutation positive, or no mutation found), and compared for significant statistical differences using paired t-tests or chi-square analysis. Differences between dermatologist and genetic counsellor reported results will also be analysed.

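### The dermatologist-versus-counsellor comparison and its follow-up dates are tied to receiving a result, which comes after randomisation, so participants who decline may be left out and have no dated behavioural follow-up

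*Protocol*

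**What the plan says.** **What is randomised.** Under Dermatologist reporting genetic results, participants "will be randomised to receive the genetic education, counselling and test reporting by either a genetic counsellor or a dermatologist". The allocation therefore covers the first counselling session as well as the reporting session.

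**What is compared.** The protocol describes this in two ways.

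- Narrow: the Data Analysis section (item 7.1) says "Differences between dermatologist and genetic counsellor reported results will also be analysed". The Introduction likewise says the study will "evaluate whether the method of delivery (dermatologist compared with genetic counsellor) of genetic test results for familial melanoma influences" outcomes.
- Wide: aim 3 in section 1.2 is to "Determine whether the person conducting the counselling session (genetic counsellor/dermatologist) affects psychosocial and behavioural outcomes". The section on dermatologist reporting adds: "Questionnaire data collected throughout stage 1 of the study will be used to analyse any significant differences in psychosocial or behavioural outcomes".

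**Decliners.** The section on participants who decline testing expects that some will "change their mind and decline genetic testing after receiving pre-testing genetic counselling and education". It also allows for people who never wanted testing and for people who are tested but refuse the result. It keeps all of them in the study: "We would ask them to still complete pre and post questionnaires". Health behaviour is among the topics those questionnaires are to cover.

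**Timing.** Section 2.3 says that post-test "questionnaires will be conducted at 2 weeks, 3 months and 12 months following reporting of test results". Table 1 gives decliners a column of their own at the second visit and at no later time point.

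**The concern.** The decision to give a saliva sample is taken at the end of the first session, with the provider to whom the participant was randomised. Whether someone ends up with a reported result is therefore partly an outcome of the allocation. A comparison restricted to people with reported results would set one selected group against another. If one type of provider led more hesitant or anxious people to decline, that arm could look better on distress simply because those people were no longer counted.

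The dating rule is a separate problem and lies in data collection. Aim 3 concerns behavioural outcomes, and the later questionnaires are where behaviour is measured. Participants without a result date have no defined time for completing them. An analysis plan written later could settle who is analysed, but it could not recover measurements that were not taken at comparable times.

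**Working it through.** The protocol gives no decline rate, allocation ratio, effect size or power for this comparison, and the Stage 1 size of about 50 depends on qualitative saturation. There is no figure to reproduce. The check is mainly textual, followed by an illustration.

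**Step 1: what decliners have under Table 1**

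| Measure | Second visit, testers | Second visit, decliners | After the second visit |
| --- | --- | --- | --- |
| Risk perception, HADS | yes | yes | 2 weeks, 3 and 12 months |
| Genetic Counselling Satisfaction Scale (GCSS) | yes | yes | 2 weeks |
| Perceived personal control (PPC), STAI, Monitor/Blunter | yes | yes | none |
| Sun exposure, skin surveillance | no | no | 3 and 12 months |
| Cancer Worry, Fatalism | no | no | 3 and 12 months |
| MICRA | no | no | 2 weeks, 3 and 12 months |

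The second visit gives anxiety, satisfaction and perceived control on the same scales for decliners and testers. Sun exposure, skin surveillance, cancer worry and fatalism have no post-baseline measurement before 3 months. All of those later points are counted from reporting of results. As written, a decliner has no dated post-baseline behavioural measure.

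**Step 2: the passages side by side**

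The Data Analysis and Introduction wording implies people who received results. Aim 3 and the section on dermatologist reporting imply everyone counselled by an allocated provider. The section on decliners asks for later questionnaires on behaviour, while section 2.3 supplies no date for them. These statements cannot all be followed literally.

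**Step 3: illustration of size**

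Assumptions: 1:1 allocation, so 25 per arm; uptake of 95% in one arm and 80% in the other; no true provider effect; and decliners differing from testers by the same D (in SD) in both arms.

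- Remaining participants: 25 × 0.95 = 23.75 (about 24) and 25 × 0.80 = 20. In the second arm 5 of 25, or 20%, are missing.
- Both arms share the same overall mean, and the mean among testers is that mean minus D × decline rate. Dropping decliners therefore creates a spurious difference of size D × (d1 − d2), where d1 and d2 are the decline rates.
- Here d1 − d2 = 0.20 − 0.05 = 0.15. D = 0.3 gives 0.045 SD, D = 0.5 gives 0.075 SD and D = 1.0 gives 0.15 SD.
- With a wider gap, 30% against 10% declining, d1 − d2 = 0.20, giving 0.06, 0.10 and 0.20 SD for the same three values of D.
- With equal decline rates the bias is zero under these assumptions.

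For scale, the difference detectable with 80% power at two-sided 5% with 25 per arm is (1.960 + 0.842) × √(2/25) = 0.79 SD.

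**The case against.** A reader might infer that decliners do drop out of the comparison and that randomisation is broken. The protocol does not support that reading.

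- No passage excludes decliners. The phrase in Data Analysis can be taken as shorthand for the two arms: the section that sets up the randomisation is itself headed by dermatologist reporting, although its text covers education and counselling too. The most specific statement about the data for this comparison draws on all of Stage 1. **This stands**, and it limits the point to a conflict of wording.
- Decliners have the same second-visit scales as testers, so short-term distress and satisfaction can be compared for everyone. **This stands**, and the gap is confined to the later questionnaires.
- Having no mutation result does not remove a decliner from the provider comparison, because the randomisation strata use family mutation status. **This stands.**
- Some people decline from the outset for reasons unrelated to the provider, so not all declining is a consequence of allocation. **This stands**, and it would reduce any imbalance between arms.
- The analysis population, and a comparison of uptake by arm, may be set out in a statistical analysis plan that is not shown. **This stands**: their absence here is not a finding. It does not answer the conflicting wording or the dating rule, both of which are in the protocol.
- The assumed biases are small beside the detectable difference of 0.79 SD, the primary aim is qualitative and the Introduction calls the provider question a pilot. **This stands** as an argument about severity.

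**Conclusion.** The point holds in a limited form. The literal wording of the comparison depends on an event after randomisation that the provider can influence, and it conflicts with aim 3 and with the section on dermatologist reporting. If it were followed literally, decliners could be left out and the protection of randomisation lost for that comparison. Separately, the follow-up schedule gives decliners no date for any post-baseline measure of sun exposure, skin surveillance, cancer worry or fatalism, although the protocol asks them for later questionnaires on health behaviour.

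The size of any bias is unknown. The figures of about 24 against 20 remaining and about 0.05 to 0.15 SD rest entirely on assumed uptake, 1:1 allocation and assumed differences between decliners and testers. If declining is rare or balanced between arms, the effect is small. Severity is moderate: the comparison is secondary and exploratory, but the remedy is cheap and the dating rule affects which data can be used.

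**What to change.** Reconcile the Introduction, section 2.3 and Data Analysis with aim 3, the section on decliners and the section on dermatologist reporting. Suggested wording:

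> The comparison of dermatologist with genetic counsellor includes every randomised participant, analysed by allocated provider, whether or not they were tested or received a result. For participants who decline testing or results, the 2-week, 3-month and 12-month questionnaires are timed from the second session, or from its scheduled date if it does not take place. Scales that require a result are reported separately, among those who received one, as a non-randomised comparison.

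Reporting uptake of testing and of results by arm would be a useful addition, since the data will exist anyway.

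The cost is a wording change and a date rule in REDCap; the protocol already intends to keep decliners and to question them. The drawback is that result-specific scales such as MICRA cannot be scored in decliners, so for those scales the provider comparison remains a subset without the protection of randomisation.

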**8.1 Interview data**

Semi-structured interviews conducted in Stage 1 of this study and Clinician Interviews will be transcribed verbatim for thematic analysis. The objective of thematic analysis is to identify the themes within participants’ responses to interview questions. The process of thematic analysis has 6 distinct steps, which are described in Braun and Clarke’s (2006) publication on ‘Using thematic analysis in psychology’:

1. Familiarisation with the data: Read and re-read interview transcripts.
2. Generating initial codes to the data: A code is a brief description of what has been said. It highlights a section of data that is interesting or relevant to the research question. Some codes will be repeated throughout the dataset on different extracts, while others may only occur once.
3. Search for themes: group codes into themes and determine how the themes connect.
4. Review themes: Read all the extracts of coded data within a theme and determine whether they support the theme, or if they are better suited to another existing or new theme. Generate a thematic ‘map’ of analysis.
5. Defining and naming themes: Assign a descriptive name for each theme and define the overall story within that theme, quoting important extracts of coded data connected to that theme.
6. Producing the report: A final analysis of interview data in the context of study objectives and current literature. It is intended to publish the reported findings of the interview data in a peer-reviewed medical/science journal.

**8.2 Stage 2: Cross-sectional Questionnaire**

Statistical methods will be used to quantitatively analyse questionnaire data. Possible answers to questions will include binary answers (e.g. yes/no), or on a 5 point Likert Scale (e.g. strongly agree, agree, unsure, disagree and strongly disagree). Total and subscale scores will be computed and tested for normality. The statistical analysis plan will be further developed upon design of the final questionnaire.

# **Data Management**

Participant data will be handled with utmost confidentiality. A participant log will be kept where a coded ID number will be allocated to each participant. Interview transcriptions, questionnaire data, saliva samples, and genetic data will only have the participant ID number on them to protect privacy. The participant log will only be accessible to the study investigators. Electronic files are stored on the University of Queensland’s secured network, and password protected. Any hardcopy paper documents will be stored in locked cabinets within the card accessed TRI building.

Questionnaire data will be recorded on the REDCap system, which is a secured study database software developed by Vanderbilt University, and administrated by the Queensland Clinical Trials and Biostatistics Centre at the School of Public Health, The University of Queensland.

# **Dissemination of results**

Results from this study are planned to be disseminated through peer-reviewed publications, conferences and non-peer reviewed media outlets. No identifiable information will be used in publication of the results. As this study is being completed as part of Associate Investigator [name]’s PhD, results of this study will also be published in her thesis. No identifiable information will be used in the thesis.

We will generate a summary of research findings from Stage 1 and 2 of the study to be provided to our participants. This summary will be submitted to the HREC for approval before sending it out. The summary will be sent via email to participants who requested to receive this information on their PICF at the start of the study.

# **Ethical considerations**

The study will be reviewed by Metro South Health HREC located at Princess Alexandra Hospital, The University of Queensland HREC and the QIMR Berghofer Medical Research Institute HREC in accordance with the *National Statement of Ethical Conduct in Human Research (2007),* the International Guidelines known as *Good Clinical Practice* and the *World Medical Association’s Declaration of Helsinki.*

All participants will receive written and verbal information about the study. This information will emphasise that participation is voluntary and that they may withdraw from the study at any time for any reason without penalty or jeopardising their medical care. All participants will be given the opportunity to ask questions and will be given sufficient time to consider before consenting.

As the study involves reporting genetic test results, there is a risk of negative psychological reaction from participants. Although we believe a positive result for a genetic mutation inferring increased risk to melanoma would not be unexpected in this cohort, it could still be upsetting. Furthermore, some of the genes included in the testing panel are associated with risk for other cancers, and this may be unexpected. If this occurs, it will be discussed appropriately with the participant by a genetic counsellor. If the participant expresses significant upset, or if it is evident to any of the research team, the participant will be offered additional counselling. Participants are also provided with contact details to the study team if they think of further questions after their appointment, or if they’d like to see a genetic counsellor for an additional appointment. Any additional counselling appointments will be provided to participants at no charge to them.

